Abbreviations: BMI= body mass index; BG= blood glucose; BP = blood pressure; HR= heart rate; BIA= bioelectrical impedance analysis; CGM=continuous glucose monitoring; DTSQs-c= diabetes treatment satisfaction questionnaire status and change versions; ECG= electrocardiogram; U/S=unscheduled; P/D= premature discontinuation; DKA=diabetes ketoacidosis; HbA1c = hemoglobin A1c; Hb= hemoglobin; HCT= hematocrit; IMP=investigational medicinal product; FDA=Food and Drug

*Administration.*

aOnly for the participants in the intervention arm.

bIncluded: gender, race/ethnicity, and year of birth.

cThe temperature should be measured at the screening visit (V1) and randomization visit (V2) to exclude infection.

dA serum pregnancy test will be performed at the screening visit, the result must be available before randomization and the first injection of the study drug for women of childbearing potential only. Additional pregnancy in urine tests will be repeated during the study (**See annex 6-6.1**).

eInclude: total bilirubin, direct bilirubin, alkaline phosphatase (ALP), partial thromboplastin time (PTT), prothrombin time (PT), international normalized ratio (INR), alanine aminotransferase (ALT), aspartate aminotransferase (AST), and gamma-glutamyl transferase (GGT). (**See annex 6-6.1**).

fInclude: total bilirubin, direct bilirubin, ALT, AST. (**See annex 6-6.1**).

gInclude: thyroid stimulating hormone (TSH), free thyroxine (FT4), calcitonin, C-peptide (fasting), estradiol, and follicle-stimulating hormone (FSH) (**See annex 6-6.1**).

hOnly calcitonin (**See annex 6-6.1**).

iInclude: creatinine (with eGFR by CKD-EPI), and urine microalbumin/creatinine ratio (uACR) (**See annex 6-6.1**).

jOnly creatinine (with eGFR by CKD-EPI) (**See annex 6-6.1**).

kThe participant also can use her/his phone if it is compatible with Dexcom G7 and the study apps.

lInclude: test strips, lancing device, and lancets.

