### 9.3 Procedures at each visit

#### 9.3.1 Visit 1 – Screening.

After informed consent is obtained, the study staff will conduct vital signs and physical evaluation (including height and weight). The following procedures may be performed, data collected, and eligibility criteria checked and documented:

- Inclusion and exclusion criteria assessed.
- Demographics (year of birth, race/ethnicity, and gender).
- Diabetes and medical history (including severe hypoglycemia, DKA history, and microvascular complications).
- Substance use history (drinking, smoking, and drug habits).
- Prior and/or concomitant medications.
- Physical examination including weight, height, waist & hip circumference, waist-to-hip ratio, and vital signs (blood pressure, heart rate, and temperature).
- Electrocardiogram (ECG)
- Serum pregnancy test (serum beta-Hcg) for all females of child-bearing potential.
- Laboratory tests including Hb, hct, total serum bilirubin, direct bilirubin, indirect bilirubin, ALT, AST, ALP, PTT, PT, INR, GGT, serum albumin, pancreatic serum amylase, serum lipase, creatinine, eGFR (calculated by CKD-EPI), urine albumin/creatinine ratio (uCR), calcitonin, TSH, FT4, fasting plasma glucose (FPG) C-peptide (fasting), estradiol and FSH (if apply), TC, LDL, HDL, and triglycerides.
- HbA1c level measured using the DCA Vantage or similar point-of-care device/local lab.
- The study participant will receive a hypoglycemia diary to document clinically significant or severe (see **Annex 10** for hypoglycemia classification) hypoglycemia events, related symptoms, and precipitating activities such as meal omission, increased exercise frequency/intensity, or any other potential causes of hypoglycemia.
- AE/SAE assessment according to **Section. 10**.

Diabetes management information: We will record the participant's average total daily insulin use and total bolus insulin use (calculated over approximately two weeks), carbohydrate ratio, and correction factor (insulin sensitivity factor). Data from the participant's glucometer and CGM may be downloaded or recorded.

The participant will receive a study phone (if needed), an activity tracker (Fitbit sense 2), and the Dexcom G7 CGM system. The study apps (Fitbit app/SNAQ app) will be installed, and participants will receive training on their use. The study handbook also will be given to the participants.

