#### Both randomization arms:

During this visit, the study team will perform the following evaluations.

- Weight, height, waist & hip circumference, waist-to-hip ratio
- Vital signs (blood pressure and heart rate)
- ECG
- Urine pregnancy test
- Device downloads (CGM and pump data)
- Apps Downloads (SNAQ App, activity tracker)

- AE/SAE assessment according to **Section. 10** (including assessment for clinically significant hypoglycemia, severe hypoglycemia, and DKA)
- The hypoglycemia diary will be collected and reviewed.
- Laboratory tests including total bilirubin, indirect and direct bilirubin, ALT, AST, pancreatic serum amylase, serum lipase, and creatinine with eGFR (calculated by CKD-EPI).

Intervention arm:

The participant's medication logbook will be reviewed, the IMP's used pen will be collected, and the study physician will configure the systems and pump's parameters if needed (**See Annex 3**).

### 9.3.5 Phone Visit 2

Both randomization arms:

During this visit, the study team will contact the participants by phone. The study staff ensures that the data from the devices (CGM and pump data) have been downloaded, the hypoglycemia diary reviewed, and perform the AE/SAE assessment, according to **Section 10**.

Intervention arm:

If needed, the study physician will configure the systems and pump's parameters (**See Annex 3**).

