#### Adjudicated hepatic or pancreatic AEs (Hepato-biliary disorders)

Hepato-biliary events will be considered AEs. All events of treatment, emergent biliary colic, cholecystitis, or other suspected events related to gallbladder disease will be evaluated, and additional diagnostic tests will be performed as needed. If a study participant experiences elevated ALT  $\geq 3X$  ULN, ALP  $\geq 2X$  ULN, or elevated TBL  $\geq 2X$ ULN, liver testing (**See Annex 9**) will be repeated within three to five days, including ALT, AST, ALP, TBL, direct bilirubin, and GGT to confirm the abnormality and to determine if it is increasing or decreasing. If the abnormality persists or worsens, clinical and laboratory monitoring will be initiated by the investigator and in consultation with the study medical monitor. ALT, AST, TBL, and ALP monitoring should continue until levels normalize or return to approximate baseline levels.

Additional safety data will be collected via the eCRF, and the IMP should be stopped if one or more of the following conditions occur:

- Elevation of serum ALT or AST  $>8$  times ULN
- Elevation ALT or AST  $>5$  times ULN for more than 2 weeks
- Elevation ALT or AST  $>3$  times ULN and TBL  $>2$  times ULN or INR  $>1.5$
- Elevation ALT or AST  $>3$  times ULN with the appearance of fatigue, nausea, vomiting, right upper-quadrant pain or tenderness, fever, rash, and/or eosinophilia ( $>5\%$ )
- Elevation ALP  $>3$  times ULN
- Elevation ALP  $>2.5$  times ULN and TBL  $>2$  times ULN
- Elevation ALP  $>2.5$  times ULN with the appearance of fatigue, nausea, vomiting, right quadrant pain or tenderness, fever, rash, and/or eosinophilia ( $>5\%$ )
- Elevated serum TBL to  $\geq 2X$  ULN (except for cases of known Gilbert's syndrome).

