## Annex 9. Liver Safety: Hepatic Evaluation testing.

Refer to **Section 10.1.2.** for guidance on appropriate definitions and follow-up assessments.

- The appropriate liver tests (beyond ALT, AST, TB, Indirect and direct bilirubin) will be selected, as needed, according to the investigators' clinical criteria.
- The test will be performed by a central laboratory, and the results will be included in the CFRs.

| Hepatic Monitoring Tests |                                    |
|---------------------------------|------------------------------------|
| Hepatic Hematology       | Hepatic Coagulation         |
| Hemoglobin                      | Prothrombin Time                   |
| Hematocrit                      | Prothrombin Time, INR              |
| RBC                             |                                    |
| WBC                             | Hepatic Serologies          |
| Neutrophils, segmented          | Hepatitis A antibody, total        |
| Lymphocytes Hepatic Serologies  | Hepatitis A antibody, IgM          |
| Monocytes                       | Hepatitis B surface antigen        |
| Eosinophils                     | Hepatitis B surface antibody       |
| Basophils                       | Hepatitis B Core antibody          |
| Platelets                       | Hepatitis C antibody               |
|                                 | Hepatitis E antibody, IgG          |
| Hepatic Chemistry        | Hepatitis E antibody, IgM          |
| Total bilirubin (TB)            |                                    |
| Direct bilirubin                | Other serologies            |
| Alkaline phosphatase            | Anti-nuclear antibody (ANA)        |
| ALT                             | Anti-smooth muscle antibody (ASMA) |
| AST                             | Anti-actin antibody                |
| GGT                             | Epstein-Barr Virus (EBV) antibody  |
| CPK                             | Epstein-Barr Virus DNA             |
|                                 | Cytomegalovirus antibody           |
| Other Chemistry          | Cytomegalovirus DNA                |
| Acetaminophen                   | Herpes Simplex Virus (HSV)         |
| Acetaminophen protein adducts   | HSV (Type 1 and 2) antibody        |
| Alkaline phosphatase isoenzymes | HSV (Type 1 and 2) DNA             |
| Ceruloplasmin                   | LKM-1 Antibody                     |

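### Alkaline phosphatase is a retest trigger and a stand-alone stopping criterion but is not scheduled after screening; separately, the week-16 fasting TG-glucose index has no scheduled fasting glucose

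*Protocol*

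**What the plan says.** **Liver safety rules.** Section 10.1.2 gives three laboratory thresholds that start a repeat panel: ALT at 3 times ULN, ALP at 2 times ULN, and total bilirubin (TBL) at 2 times ULN. Liver testing then "will be repeated within three to five days, including ALT, AST, ALP, TBL, direct bilirubin, and GGT to confirm the abnormality". It adds that "the IMP should be stopped if one or more of the following conditions occur", followed by eight conditions. Three involve ALP: above 3 times ULN alone, above 2.5 times ULN with raised TBL, and above 2.5 times ULN with symptoms.

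**Liver tests scheduled.** At screening, section 9.3.1 has "Laboratory tests including Hb, hct, total serum bilirubin, direct bilirubin, indirect bilirubin, ALT, AST, ALP, PTT, PT, INR, GGT, serum albumin", and footnote e to Table 1 also names ALP. For Visits 3 and 4, footnote f has "Include: total bilirubin, direct bilirubin, ALT, AST". Section 9.3.4 (Visit 3) has "Laboratory tests including total bilirubin, indirect and direct bilirubin, ALT, AST, pancreatic serum amylase, serum lipase, and creatinine with eGFR". The Visit 4 list in 9.3.6 names the same liver tests, again without ALP.

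**Other routes to an ALP value.** Section 10.1.2 says that biliary colic, "cholecystitis, or other suspected events related to gallbladder disease will be evaluated, and additional diagnostic tests will be performed as needed". Annex 9 says "The appropriate liver tests (beyond ALT, AST, TB, Indirect and direct bilirubin) will be selected, as needed", at the investigator's clinical judgement. Section 9.3.8 allows unscheduled visits.

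**TG-glucose index.** Section 5 lists it, in the fasting state, among exploratory outcomes compared between groups at week 16. Table 1 marks the fasting lipid panel at Visits 1 and 4 but fasting glucose at Visit 1 only. The screening list in 9.3.1 includes "fasting plasma glucose (FPG) C-peptide (fasting), estradiol and FSH (if apply), TC, LDL, HDL, and triglycerides"; the Visit 4 list has triglycerides and no glucose.

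**The concern.** A stopping rule protects participants only if the quantity it depends on is measured while stopping is still possible. Here one rule rests on ALP alone, yet no scheduled blood test during dosing includes ALP. The protocol itself names cholelithiasis and cholecystitis as rare drug risks (3.7), counts hepatic events among its safety outcomes, and has no data safety monitoring committee.

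The TG-glucose gap is of another kind: a listed outcome lacks one of its two laboratory inputs at the time it is to be compared. An analysis plan cannot supply a test that was never drawn. Section 12.6 says samples are not stored, so the assay cannot be run later, and 11.5 rules out imputation.

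**Working it through.** No published figure has to be reproduced. The check sets the schedule beside the rules and outcomes that depend on it.

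**Step 1. Scheduled laboratory draws after randomisation.** Table 1 has two, Visit 3 (week 8) and Visit 4 (week 16). The contacts at weeks 4 and 12 are by phone, and at Visit 2 the only listed laboratory test is a urine pregnancy test. Visit 4 is the end of intervention, so one draw, Visit 3, can inform a decision to stop.

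**Step 2. Inputs against schedule** (Table 1 and footnotes, 9.3.1, 9.3.4, 9.3.6).

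| Test | Visit 1 | Visit 3 | Visit 4 |
|---|---|---|---|
| ALT, AST, total and direct bilirubin | yes | yes | yes |
| ALP | yes | no | no |
| Fasting triglycerides | yes | no | yes |
| Fasting glucose | yes | no | no |

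ALP is therefore in 0 of 1 scheduled draws during dosing. For the TG-glucose index, 2 of 2 laboratory inputs are scheduled at Visit 1 and 1 of 2 at Visit 4. The premature-discontinuation visit mirrors Visit 4 (9.3.8) and has the same gaps.

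**Step 3. Which ALP rules are affected.**
- ALP above 2.5 times ULN with TBL above 2 times ULN: reachable. TBL is scheduled at Visit 3, and TBL at 2 times ULN requires a repeat panel that contains ALP. That TBL level is also a stop criterion by itself, except in known Gilbert's syndrome.
- ALP above 2.5 times ULN with symptoms: reachable through symptom-led evaluation or added liver tests.
- ALP above 3 times ULN alone: reachable only if raised ALT or TBL starts the repeat panel, symptoms prompt testing, or the investigator chooses to test. If none applies, it is missed.
- ALP at 2 times ULN as a retest trigger: the same limitation.

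What is left uncovered is an isolated, asymptomatic ALP rise with ALT below 3 times and TBL below 2 times ULN.

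**Step 4. Assays needed.** ALP at Visit 3: 1 × 42 = 42. Fasting glucose at Visit 4: 1 × 42 = 42. Total 42 + 42 = 84. With optional ALP at Visit 4: 84 + 42 = 126.

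**The case against.** **The lists may not be exhaustive.** Footnote f begins with a non-exclusive verb, whereas footnotes h and j restrict themselves explicitly to one test. Footnote f also omits indirect bilirubin, which 9.3.4 and 9.3.6 require, and footnote e omits albumin, which 9.3.1 requires. This weakens footnote f as sole proof. It does not close the gap, because footnote e, for the same table row and with the same verb, names ALP, footnote f does not, and both visit lists agree with footnote f. Annex 6.1 omits ALP too, but it also drops creatinine and fasting glucose that Table 1 schedules, so it is not relied on here.

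**The ALP gap is narrow.** This stands. A reader might infer that ALP is never measured on treatment, or that all three ALP stop criteria are dead letters. The repeat panel, the symptom-led route and Annex 9 show otherwise. The documents give no rate for isolated ALP rises and describe no such signal with tirzepatide.

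**Glucose could come from the sensor.** Section 8.10.1 makes the study CGM the reference for blood glucose, and an analysis plan could choose the source. The protocol does not name it for this index, however, and a week-16 sensor reading would be set against a screening plasma value obtained by another method.

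**FIB-4.** A reader might also infer that FIB-4, another week-16 exploratory outcome, cannot be computed because platelets appear only in the Annex 9 list. The protocol prints no formula or inputs for FIB-4, so the documents do not support that conclusion. The TG-glucose index has no printed formula either, but its name states both inputs and the fasting condition.

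**Conclusion.** The point holds in two limited parts. First, scheduled testing at week 8 would not detect an isolated, asymptomatic ALP rise, although the protocol treats such a rise as reason to retest and, above 3 times ULN, to stop. The stop rule concerns the 21 participants allocated to tirzepatide. The size is stated as coverage (0 of 1 scheduled draws during dosing), because nothing in the documents allows an expected number of missed cases to be calculated. Second, one exploratory index lacks a scheduled laboratory glucose at week 16 for all 42 participants; triglycerides remain analysable as an outcome of their own.

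This assumes that sites draw what the visit lists name and that Visit 4 falls at week 16 as in Table 1. The primary and hierarchical secondary outcomes do not depend on any of these tests. It is a safety-monitoring and schedule inconsistency that merits a small amendment and does not threaten the main result.

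**What to change.** Add ALP to the Visit 3 draw in both arms. ALP at Visit 4 is optional: it comes too late to inform stopping but completes the end-of-treatment safety record. Add fasting plasma glucose to the Visit 4 draw, which is already fasting for lipids, or delete the TG-glucose index. Align Table 1 and its footnote f, sections 9.3.4 and 9.3.6, and Annex 6.1, whose creatinine and screening-glucose omissions should be corrected at the same time.

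The cost is 84 routine assays, or 126 with ALP at Visit 4, on blood draws already planned and with no new visit. ALP is costed for all 42 participants although only 21 take the drug, because 11.4.5 compares adverse events between arms and testing one arm alone would make detection unequal.

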### **Data Safety Monitoring Committee**

Not applicable.

## 2. ETHICAL AND REGULATORY ASPECTS

Type 1 diabetes (T1D) is a chronic disease with an increasing incidence and prevalence (1–3). Intensified insulin treatments have led to a significant reduction in the risk of development and progression of long-term microvascular complications in T1D (4,5). However, this intensification also leads to more hypoglycemia events and weight gain with an increase in cardiovascular risk factors (6,7).

This study will test the safety and efficacy of the dual glucose-dependent insulinotropic polypeptide/glucagon-like peptide-1 receptor agonist (GIP/GLP1-RA) (*Mounjaro*® [tirzepatide]) as an adjunct therapy in people with T1D with existing insulin therapy through automated insulin delivery (AID). The results of this study will make an important contribution to the care of patients with T1D by improving their self-management, reducing the T1D burden, and improving their quality of life. The trial may result in improved glucose control and weight loss for the participants, indicating the potential for this molecule to become part of standard care for T1D in the future. Participants will be provided with written informed consent and fully informed about the study, including the risk-benefit ratio (**See Section 3.1**). Their right to stop the procedures and withdraw the informed consent at any time during the study will be respected.

The sponsor will submit the protocol, the proposed patient information and consent form, and other study-specific documents to the “Ethikkommission Nordwest-und Zentralschweiz” (EKNZ) and Swissmedic before the study commencement. The clinical study will only begin once approval from all required authorities has been received. Any additional requirements imposed by the authorities will be implemented.

### 2.1 Study registration

This study will be registered at [www.clinicaltrials.gov](http://www.clinicaltrials.gov) and in the Swiss National Clinical Trial Portal (SNCTP) at [www.kofam.ch](http://www.kofam.ch).

### 2.2 Categorization of Study

This study examines the safety and feasibility of adding a medicinal product as adjunctive therapy to AID in T1D. The investigational medicinal product (IMP) is authorized in Switzerland for treating people with type 2 diabetes (T2D) but will not be used as intended in Paragraph 1 of Chapter 2, Article 19 of ClinO (8,9). Therefore, the study is classified under Category B according to the Swiss HRA and its corresponding Ordinance Clin-O on clinical trials.

### 2.3 Competent Ethics Committee (CEC)

The Sponsor will submit the investigation to the corresponding CEC to obtain Ethical approval before the investigation starts. The Sponsor and the principal investigator (PI) will also ensure that approval from the CEC is obtained and filed in the investigator site file (ISF) before starting the trial.

No protocol changes are made without the sponsor's and the CEC's prior approval, except when necessary to eliminate immediate hazards to study participants.

The premature end or interruption of the study will be reported within 15 days. The regular end of the study will be reported to the CEC within 90 days; the final study report will be submitted within one year after the study ends. Amendments are reported according to **Section 2.10**.

### 2.4 Competent Authorities (CA)

The Sponsor will submit the investigation to the CA for approval before the clinical trial starts. The Sponsor ensures that approval from the CA is obtained and filed in the investigator site file before the commencement of the study (**See Section 2.2**).

Premature study termination or interruption and the regular end of the study will be reported within the same timeline as for CEC (**See Section 2.3**), except for non-substantial amendments that will be reported as soon as possible. For Amendments, **see Section 2.10**.

### 2.5 Ethical Conduct of the Study

The study will be carried out following the protocol and with principles enunciated in the current version of the Declaration of Helsinki (10), the guidelines of Good Clinical Practice (GCP) issued by the International Conference on Harmonization (ICH) (11), and Swiss Law and Swiss regulatory authority's requirements (8). The CEC and regulatory authorities will receive the Annual Safety Report (ASR) and interim reports and be informed about the study stop/end in agreement with local requirements.

## 2.6 Declaration of Interest

This study is an MD-PhD thesis. The Sponsor supervises the MD-PhD student, who has been actively involved in the study design, protocol development, and documentation preparation for ethics submission. The student will be present at the study site and will participate in recruitment, data collection, study assessments, data analysis, and scientific writing for future publications.

## 2.7 Patient Information and Informed Consent

The PI (or his designee) will explain to each participant the nature of the study, its purpose, the procedures involved, the expected duration, the potential risks and benefits, and any discomfort it may entail. Each participant will be informed that participation in the study is completely voluntary, that he/she may withdraw from the study at any time, and that withdrawal of consent will not affect his/her subsequent medical assistance and treatment.

The participants will be informed that they can ask any questions and consult with family members, friends, their treating physicians, or other experts before deciding to participate in the study. The study participants will be given enough time (about 1 to 3 days). If the participant needs further time, it will be conceded (12).

The participants will be informed that authorized individuals other than their treating physician may examine his/her medical records.

All participants will receive a participant information sheet and a consent form, which will describe the study and provide sufficient information for them to make an informed decision about their participation. The formal consent of a participant, using the approved consent form, will be obtained before the participant is subject to any investigation procedure.

The participant should read, understand, and voluntarily agree before signing and dating the informed consent form. The consent form will be also signed and dated by the PI (or her/his designee). The signed consent form will be retained as part of the investigation records. The participant receives a copy of the signed document.

It is the responsibility of the PI (or her/his designee) to document in detail the information procedure and consenting process in the participant's medical record or other suitable source data.

